## Abstract

**Background:**

Diabetic peripheral neuropathy (DPN) is a length-dependent, symmetric sensorimotor polyneuropathy with a substantial global and regional burden. Current pharmacologic options are largely symptomatic and do not modify the disease. Lymphovenous bypass (LVB), a supermicrosurgical procedure established for lymphedema, may modulate lymphatic-immune-microvascular dysfunction relevant to DPN.

**Objective:**

The primary objective is to determine whether LVB combined with standard of care (SOC) improves small-fiber and autonomic function compared with SOC alone at 6 months. Secondary objectives are to evaluate the effects of LVB on large-fiber function, neuropathic pain, ulcer healing, quality of life, and relevant biomarkers, as well as to characterize the safety profile of LVB.

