**Methods:**

This is a SPIRIT (Standard Protocol Items: Recommendations for Interventional Trials)–aligned, single-center, randomized, controlled, parallel-group superiority trial with a 2:1 allocation (LVB+SOC vs SOC alone). Randomization is stratified based on the presence or absence of active diabetic foot ulcers, as defined by the International Working Group on the Diabetic Foot and Infectious Diseases Society of America criteria. In total, 60 adults aged 20 to 80 years with confirmed DPN will be enrolled. LVB involves lymphatic-venous anastomosis to venules ≤0.8 mm. SOC consists of guideline-based glycemic and risk-factor management, pain control, and standardized wound care. Outcome assessors and statisticians are blinded. The primary outcomes are changes in clinical neuropathy burden and pain severity at 6 and 12 months. Secondary outcomes comprise objective measures of somatic and autonomic physiology, histopathological nerve fiber density, biological serum markers, and longitudinal ulcer epithelialization parameters. Data analysis will use mixed-effects models for repeated measures, with a sample size of 60 adults providing 80% power to detect a conservative between-group effect size of Cohen *d*=0.70.

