### Randomization, Allocation Concealment, and Blinding

Participants will be randomized using a computer-generated permuted block design with variable block sizes of 3 and 6. To ensure structural balance, randomization will be stratified within the REDCap module into 2 parallel sequences: stratum 1 (active ulcer present: Wagner grade ≤2) and stratum 2 (no active ulcer). Upon coordinator registration, the participant’s clinical ulcer status will automatically determine the next sequential allocation exclusively from the corresponding stratum block. Neither participants nor surgeons will be blinded due to the nature of the intervention; however, outcome assessors and statisticians will remain blinded to group allocation. To minimize the risk of unblinding, standardized dressings will be used across groups, and independent assessors will conduct outcome evaluations. The enrollment, randomization, intervention, and follow-up processes are summarized in Figure 1 and Table 1.

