#### Control Intervention (SOC Alone)

Participants assigned to the control arm will receive SOC only, consisting of guideline-based glycemic and cardiovascular risk-factor management, neuropathic pain control, footwear or offloading, and standardized wound care for those with ulcers. No sham procedure will be performed owing to ethical considerations.

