### Outcomes

The primary objective is to compare LVB+SOC with SOC alone in terms of changes in neuropathic pain, assessed by the DN4 questionnaire, and DPN burden, measured by the MNSI at 6 and 12 months. Secondary objectives are to evaluate sudomotor function using Sudoscan, large-fiber nerve conduction parameters, and, in participants with ulcers, time to complete epithelialization adjudicated by blinded review, the proportion of ulcers healed by 20 weeks, infection episodes, reoperations, and rates of minor or major amputation. Exploratory objectives include assessment of serum oxidative stress and antioxidant indices, inflammatory cytokine profiles, and IENFD. The safety objective is to characterize adverse events, serious adverse events, surgical site complications, and hypersensitivity reactions to intraoperative mapping dyes [24].

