Several limitations must be acknowledged. The single-center design may constrain generalizability, and the inability to blind participants and surgeons introduces a risk of performance bias, although this limitation is mitigated by the use of objective, assessor-blinded measures such as ESC and NCS. The heterogeneity of DPN phenotypes, including the broad age range (20-80 years) included in our eligibility criteria, presents additional challenges in interpreting subgroup responses; however, our statistical model adjusts for age and diabetes duration to mitigate this issue. Although the sample size is adequately powered for the primary end point, it may be underpowered to detect smaller effects across secondary and exploratory outcomes. The small sample size, particularly in the SOC control group (n=20), poses a significant constraint relative to the planned complex multivariable MMRM analyses and increases the risk of unstable estimates. Future research should include multicenter replication to validate findings, cost-effectiveness analyses to assess feasibility in routine practice, and refinement of indications such as early autonomic DPN or refractory ulcer phenotypes. Comparative effectiveness studies, including evaluation alongside emerging pharmacologic agents such as glucagon-like peptide-1 receptor agonists, are also warranted. Taken together, this trial has the potential to establish LVB as a paradigm-shifting intervention that redefines the therapeutic landscape of DPN.

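### The article states two incompatible primary objectives, and the analysed one (DN4 and MNSI) cannot establish the small-fiber and autonomic claim or use the bias protection credited to ESC and NCS

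*Protocol article*

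**What the plan says.** The Abstract (Objective) sets the primary question as whether adding lymphovenous bypass (LVB) to standard of care (SOC) "improves small-fiber and autonomic function compared with SOC alone at 6 months". It then lists pain among the secondary aims: "Secondary objectives are to evaluate the effects of LVB on large-fiber function, neuropathic pain, ulcer healing, quality of life, and relevant biomarkers".

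The next paragraph of the Abstract (Methods) says: "The primary outcomes are changes in clinical neuropathy burden and pain severity at 6 and 12 months". The Outcomes section states its own primary objective, namely "changes in neuropathic pain, assessed by the DN4 questionnaire, and DPN burden, measured by the MNSI at 6 and 12 months", and makes sudomotor function by Sudoscan secondary. The Aim of the Study and the Statistical Analysis follow the Outcomes section and place ESC, SSR, HRV and QST among the secondary measures. The Follow-Up Assessments section puts the primary end point at 6 months and treats 12 months as durability.

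On blinding: "Neither participants nor surgeons will be blinded due to the nature of the intervention". On the control arm: "No sham procedure will be performed owing to ethical considerations". Outcome assessors and statisticians are blinded. The Discussion admits a risk of performance bias and says "this limitation is mitigated by the use of objective, assessor-blinded measures such as ESC and NCS".

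**The concern.** Pain is secondary in one statement of the objective and primary in the other. Sudomotor and autonomic function is the reverse. This is not an effect of shortening a longer protocol: the article states both versions outright, and no unseen document can make both true.

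Two things are at stake. First, while two primary objectives stand, the headline can be chosen after the results are known. Second, the Discussion already anticipates a small-fiber and autonomic finding, whereas the confirmatory analysis concerns scales that the Baseline Assessments section itself describes as symptom scoring. Participants who know whether they had surgery supply at least part of those scores. The bias protection named in the Discussion belongs to other measures.

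**Working it through.** No figure in the plan settles this point, so the check sets the passages side by side.

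| Place | Primary quantity | Primary time | Small-fiber and autonomic measures |
|---|---|---|---|
| Abstract, Objective | Small-fiber and autonomic function | 6 months | Primary (pain secondary) |
| Abstract, Methods | Neuropathy burden and pain | 6 and 12 months | Secondary |
| Aim of the Study | DN4 and MNSI | 6 and 12 months | Secondary |
| Outcomes | DN4 and MNSI | 6 and 12 months | Secondary (Sudoscan) |
| Follow-Up Assessments | Not singled out | 6 months; 12 months is durability | Not ranked |
| Statistical Analysis | DN4 and MNSI jointly | 6 and 12 months | Secondary |

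1. **Objective.** Of the five places that name a primary quantity, four name pain and neuropathy burden. The Abstract's Objective stands alone.

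2. **Time point.** Two places say 6 months and four say 6 and 12 months. The Follow-Up Assessments section therefore sides with the Abstract's Objective on timing.

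3. **What a positive primary result shows.** It would show a difference in DN4 and MNSI. The Abstract's Objective lists pain separately from small-fiber and autonomic function, so by its own terms a change in pain is not a demonstration of that function. The measures that would show it are analysed as secondary.

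4. **Which measures carry the claimed mitigation.** ESC is scheduled at baseline, 6 and 12 months (Table 1) but is secondary. NCS is ticked at baseline only in Table 1 and is absent from the 6- and 12-month lists under Follow-Up Assessments. Neither protects the primary analysis.

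5. **Power.** The stated 80% (40 versus 20, d = 0.70, two-sample t test) is attached to the primary end point. Recomputed with all 60 evaluable, power is 71.0% two-sided and 81.1% one-sided. After 15% loss (0.85 × 40 = 34 and 0.85 × 20 = 17) it is 63.7% and 75.1%. That discrepancy is a separate matter. What counts here is that no effect size or power is given for ESC, SSR, HRV or QST, and that the Discussion concedes possible low power for smaller effects on secondary outcomes.

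6. **Illustration only: what an expectation effect could do.** Suppose there is no true effect, but knowledge of allocation shifts a score by b standard deviations in favour of surgery. The chance of a significant two-sided t test at 0.05 is the power at d = b, with noncentrality b × √(n₁n₂/(n₁+n₂)). The root is √(800/60) = 3.65 for 40/20 and √(578/51) = 3.37 for 34/17.

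| Assumed b | 40/20 | 34/17 |
|---|---|---|
| 0 | 5% | 5% |
| 0.3 | 19.0% | 16.8% |
| 0.5 | 43.5% | 37.9% |

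The values of b are assumptions with no source in the documents. Steps 1 to 4 do not depend on them.

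**The case against.** The strongest reply is that the Outcomes section does contain a primary objective matching the outcomes and the analysis: "The primary objective is to compare LVB+SOC with SOC alone in terms of changes in neuropathic pain, assessed by the DN4 questionnaire", together with MNSI. On that reading the trial is coherent and one paragraph of the Abstract is out of line. This stands. It makes the defect a contradiction to be resolved, and it shows which way most of the text already points.

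Second, running the trial open-label without a sham is a disclosed choice with an ethical reason given, and the Discussion acknowledges the bias. This also stands; the point does not ask for a sham.

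Third, DN4 and MNSI may not be wholly patient-answered. The Abstract and the Aim describe MNSI as a measure of neuropathy burden, and the article does not say how much a blinded assessor contributes to either score. Any assessor-scored part would be better protected. It remains true that a blinded assessor cannot blind the participant's own answers.

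Fourth, the Discussion does not say in so many words that ESC and NCS protect the primary analysis. But the sentence answers the limitation of unblinded participants without naming the scales most exposed to it, so it reads as broader cover than the design provides.

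Fifth, the article is not uniform on NCS. The Outcomes section makes nerve conduction a secondary objective and Design and Setting names NCS technicians among the blinded assessors, yet no follow-up NCS is scheduled. That inconsistency needs its own correction; it does not rescue the mitigation claim.

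**Conclusion.** The contradiction is real and should be resolved before more participants are enrolled. The Abstract's Objective conflicts with four other places on the primary quantity and with the same four on the time point. As analysed, a positive trial would support a statement about DN4 and MNSI, subject to open-label bias. It would not establish the Abstract's objective or the small-fiber and autonomic finding anticipated in the Discussion. The mitigation credited to ESC and NCS does not reach the primary analysis.

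A reader might infer three stronger things that the documents do not support:

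- **That a positive trial could support no claim of its own.** The objective in the Outcomes section matches the analysed end point, and the small-fiber and autonomic measures are still analysed and can give supportive evidence.
- **That the false-positive rate is 17% to 44%.** Those figures follow only from the assumed shifts of 0.3 and 0.5 SD. They show what a bias of that size would do, not that it is likely at 6 or 12 months.
- **That ESC must become the primary end point.** That is a trade-off for the sponsor, and nothing in the documents shows it would be feasible at 60 participants.

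The conclusion rests only on the article's own statements about objectives, outcomes, blinding and schedule.

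**What to change.** Before further enrolment, state one primary objective and one primary time point, and use them throughout the Abstract, Aim, Outcomes, Follow-Up Assessments, Statistical Analysis and Discussion. As the analysis now stands:

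- Reword the Abstract's Objective and the anticipated finding in the Discussion as effects on neuropathic symptoms and neuropathy burden, measured by DN4 and MNSI.
- Label small-fiber and autonomic results (ESC, SSR, HRV, QST) as secondary and supportive.
- Choose the time point. If it is 6 months, as the Abstract's Objective and the Follow-Up Assessments section have it, 12 months becomes a durability outcome and the Statistical Analysis must say so.
- Correct the limitation paragraph: the primary scales remain exposed to expectation bias, and ESC mitigates it only for secondary outcomes. Remove NCS from that sentence unless follow-up NCS is scheduled.

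The cost is a text amendment with 3 of 60 participants enrolled and, by the article's account, no outcome data available, so the choice would not be driven by results. The downside is a narrower headline claim.

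Making an instrument-based measure such as ESC primary is an option, with conditions. It would need its own effect size, variance and power statement. The Aim assigns ESC to sudomotor function and HRV to cardiovascular autonomic regulation, so the objective would still have to be narrowed to match. Baseline Sudoscan may be up to 3 months old, and 6-month testing is under self-payment arrangements; both bear on how complete and comparable the data would be. A rule that ESC merely point the same way as DN4 and MNSI would add little: if ESC were unaffected, its sign would agree about half the time by chance.

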**Methods:**

This is a SPIRIT (Standard Protocol Items: Recommendations for Interventional Trials)–aligned, single-center, randomized, controlled, parallel-group superiority trial with a 2:1 allocation (LVB+SOC vs SOC alone). Randomization is stratified based on the presence or absence of active diabetic foot ulcers, as defined by the International Working Group on the Diabetic Foot and Infectious Diseases Society of America criteria. In total, 60 adults aged 20 to 80 years with confirmed DPN will be enrolled. LVB involves lymphatic-venous anastomosis to venules ≤0.8 mm. SOC consists of guideline-based glycemic and risk-factor management, pain control, and standardized wound care. Outcome assessors and statisticians are blinded. The primary outcomes are changes in clinical neuropathy burden and pain severity at 6 and 12 months. Secondary outcomes comprise objective measures of somatic and autonomic physiology, histopathological nerve fiber density, biological serum markers, and longitudinal ulcer epithelialization parameters. Data analysis will use mixed-effects models for repeated measures, with a sample size of 60 adults providing 80% power to detect a conservative between-group effect size of Cohen *d*=0.70.

**Results:**

Recruitment commenced in February 2026 and is planned to continue through July 31, 2027, with follow-up through July 31, 2028. As of May 2026, we have enrolled 3 participants. The first participant has been treated, and a second participant is scheduled to undergo treatment. Data analysis and reporting are anticipated between late 2027 and early 2028. No outcome data are included.

**Conclusions:**

This trial tests a mechanism-based, nonpharmacologic adjunct targeting lymphatic-immune-microvascular dysfunction in DPN. If effective, LVB could inform phenotype-directed treatment algorithms and motivate multicenter evaluation and health economic analyses.

## Introduction

### Background

Diabetic peripheral neuropathy (DPN) is a pervasive and debilitating complication of diabetes that causes significant morbidity and increases the risk of foot ulcers and amputation [1-5]. Its prevalence in Taiwan and neighboring regions is estimated to range from 28.5% to 36.3% [6-8]. Consensus frameworks integrate staged clinical definitions with multimodal diagnostics, including symptom scales (Douleur Neuropathique 4 [DN4], ID-Pain, and Brief Pain Inventory–DPN), bedside sensory testing, autonomic and small-fiber assessments (Sudoscan and electrochemical skin conductance [ESC]), corneal confocal microscopy, quantitative sensory testing (QST), and electrodiagnostics (nerve conduction velocity–electromyography) [9-12]. Despite optimized metabolic care, more than 40% of patients may experience disease progression within 5 years [5]. Analgesics (eg, pregabalin and duloxetine) alleviate painful DPN but do not reverse neuropathy; tricyclic antidepressants require cautious use, and opioids are not first-line therapies [13,14]. Emerging agents such as glucagon-like peptide-1 agonists show preliminary structural neural benefits but require further validation [15]. This creates a critical clinical gap in which existing treatments fail to modify the underlying pathophysiology of the disease, leaving patients at risk of progressive nerve damage and secondary complications.

### Aim of the Study

The aim of this study is to evaluate whether LVB combined with standard of care (SOC) provides superior outcomes compared with SOC alone in patients with DPN. We hypothesize that restoration of lymphatic-venous drainage and modulation of inflammatory and oxidative pathways will enhance small-fiber and autonomic function, reduce neuropathic pain, and accelerate ulcer healing when present. To test this hypothesis, the primary outcomes—changes in DN4 and overall neuropathy burden (as measured by the Michigan Neuropathy Screening Instrument [MNSI]) scores—will be evaluated at 6 and 12 months. These outcomes are directly linked to secondary objective measures evaluating somatic and autonomic physiology, including small-fiber sudomotor function (ESC and sympathetic skin response [SSR]), cardiovascular autonomic regulation (heart rate variability [HRV]), thermal and vibratory thresholds (QST), and large-fiber electrodiagnostics (nerve conduction studies [NCSs]). In participants with ulcers, the impact on wound repair will be examined through time to complete epithelialization, healing rates, and complication profiles. Mechanistic insights will be explored through biomarkers of oxidative stress, immune modulation, and intraepidermal nerve fiber density (IENFD), while safety assessments will ensure the tolerability of the intervention.

## Methods

### Design and Setting

This study is a SPIRIT (Standard Protocol Items: Recommendations for Interventional Trials)–compliant, single-center, randomized, controlled, parallel-group superiority trial with a 2:1 allocation ratio (LVB+SOC vs SOC alone). Participants will be stratified based on whether they have an active diabetic foot ulcer—explicitly classified as Wagner Grade ≤2 according to International Working Group on the Diabetic Foot (IWGDF) and Infectious Diseases Society of America (IDSA) criteria—or do not have an active ulcer at the time of enrollment. This uneven allocation maximizes exposure to the novel LVB intervention, prioritizing robust safety and efficacy data for the experimental arm while maintaining a valid and adequately powered control group. Outcome assessors, including Sudoscan and NCS technicians, as well as statisticians will remain blinded to group assignment. The trial will be conducted within the National Taiwan University Hospital system, encompassing both outpatient and inpatient wound care and diabetes clinics.

### Ethical Considerations

The protocol has been approved by the National Taiwan University Hospital Research Ethics Committee (202503048RINA). Prior to any study-related procedures, written informed consent will be obtained from all participants, with an optional component for biospecimen collection. To safeguard privacy and confidentiality, study data will be captured using electronic case report forms in Research Electronic Data Capture (REDCap) with full audit trails, using pseudonymized identifiers to ensure that the data remain deidentified. Continuous safety oversight will be provided by an independent Data and Safety Monitoring Board (DSMB). Our trial has been registered in ClinicalTrials.gov website (NCT07126197). We provide each participant with a convenience store gift card valued at 2000 New Taiwan Dollars (US $64).

### Recruitment and Eligibility

Participant recruitment commenced in February 2026 and is expected to conclude by July 31, 2027, with each participant followed for 12 months. Eligible individuals will be adults aged 20 to 80 years with clinically and electrodiagnostically confirmed DPN, after exclusion of nondiabetic causes, with or without diabetic foot ulcers as defined by the IWGDF and IDSA. Participants must be able to comply with study procedures and provide written informed consent, with optional consent for biospecimen collection. Key exclusion criteria include autoimmune disease or systemic immunosuppression; clinically significant organ failure (cardiac, pulmonary, renal, or hepatic); ankle-brachial index <0.9; baseline infection requiring at least a forefoot amputation; significant cognitive impairment; pregnancy; contraindications to anesthesia or surgery; and known hypersensitivity to blue dyes, including patent blue V or indocyanine green. Recruitment will be conducted through endocrinology, neurology, and wound care clinics, as well as inpatient services. Screening procedures include medical history, DPN staging, validated symptom scales, bedside sensory testing, ESC measurement using Sudoscan, and NCS-electromyography, as indicated. Written informed consent, available in Mandarin and English, will be obtained before initiation of any study-related procedures.

### Randomization, Allocation Concealment, and Blinding

Participants will be randomized using a computer-generated permuted block design with variable block sizes of 3 and 6. To ensure structural balance, randomization will be stratified within the REDCap module into 2 parallel sequences: stratum 1 (active ulcer present: Wagner grade ≤2) and stratum 2 (no active ulcer). Upon coordinator registration, the participant’s clinical ulcer status will automatically determine the next sequential allocation exclusively from the corresponding stratum block. Neither participants nor surgeons will be blinded due to the nature of the intervention; however, outcome assessors and statisticians will remain blinded to group allocation. To minimize the risk of unblinding, standardized dressings will be used across groups, and independent assessors will conduct outcome evaluations. The enrollment, randomization, intervention, and follow-up processes are summarized in Figure 1 and Table 1.

